### Intervention

During the intervention time period, pregnant women who come for their first ANC visit at the HP will receive standard individual care. At the end of this first ANC visit, eligible women who agree to participate in G-ANC will be added to the G-ANC cohort. Approximately eight to 10 women will be enrolled in a cohort. Cohort membership will be fixed (i.e., the same women and facilitators at each meeting). Two additional pregnant women who meet study criteria can be added to a G-ANC cohort if added to the cohort by the start of the second G-ANC meeting. Six monthly G-ANC meetings will be conducted for each cohort on a fixed day/time at each HP. Each cohort will meet for G-ANC meetings in a designated meeting space that is set up to ensure privacy during clinical consultations. The G-ANC meeting will be conducted by at least one HEW who is trained in the G-ANC service delivery model.

Each meeting will have the same general structure: self-assessment by the clients/peer-to-peer self-assessment initially taught and supervised by the HEW, such as measurement of weight and blood pressure using an automated cuff; individual assessments/clinical care by the HEW in a private space; discussions around pre-determined and appropriate gestational-age themes using illustrative cards and take-home booklets designed for G-ANC; and plan/reflect and peer-support activities that create group cohesion.
Table 2 presents the G-ANC meeting schedule and content per meeting. Each meeting is expected to last 90–120 minutes and will be documented as an ANC contact. Social distancing in response to COVID-19 as per national guidelines will be enforced during meetings. Women will have the opportunity for additional private time with the HEW after the G-ANC meeting if desired or needed for health and/or safety. Women will be told that they can and should return at any time if they have questions or concerns. Phone/text reminders will be used to remind participants of G-ANC meetings as a strategy to improve ANC attendance.

**Table 2. T2:** G-ANC intervention meeting schedule.

Meetings	Timing (gestational age)	Theme/Meeting Plan
Meeting 1	4–5 months	• Introduction to group care • Preventing problems in pregnancy • Teach self-assessments
Meeting 2	5–6 months	Danger signs during pregnancy • Sexually transmitted infection (STI) transmission and partner communication/negotiation
Meeting 3 partners encouraged to attend	6–7 months	• STI transmission and partner testing • Birth plan, complication readiness • Healthy timing and spacing of pregnancy
Meeting 4	7–8 months	• Danger signs during labor and preventing problems after birth
Meeting 5	8–9 months	• Danger signs after birth
Meeting 6	9+ months	• Newborn care and danger signs

The G-ANC intervention will be implemented at the HPs that offer integrated point-of-care testing (POCT) to screen for anemia, syphilis, and asymptomatic bacteriuria. Availability of these rapid test kits improves the quality of ANC and reduces the need for women to travel to the HC for routine screening. The POCT approach was introduced by Enhancing Nutrition and Antenatal Infection Treatment (ENAT) (
Mekonnen *et al.*, 2023;
Sawtell *et al.*, 2023), a project initiated before this study as proof of concept for ANC service decentralization to the community/HP level. In ENAT, HPs started provision of the complete package of ANC services, including tests not provided at non-ENAT intervention HPs in the country or during standard care at the HP level nationally. The study provided test kits to all HPs for the duration of the study.

The G-ANC intervention and materials were adapted from Jhpiego’s G-ANC intervention model, which consisted of five monthly two-hour meetings with clinical assessments alongside structured group discussions and activities that were facilitated by nurses, midwives, or community HEWs (
Grenier *et al.*, 2019). It was modified in collaboration with the MOH for the Ethiopian context as a six-meeting model. The model is designed to increase early entry into ANC and retention in ANC in support of changes to the Ethiopian national ANC guidelines, which increased ANC contacts from four to eight contacts (
Ministry of Health Ethiopia, 2022). Intervention materials in Amharic language include a pictorial self-assessment card women use at the beginning of each meeting to record weight, blood pressure, and any danger signs; meeting guide used by the facilitators to guide each meeting; five to six A4-size illustrated picture cards per meeting that are designed for nonliterate audiences (total 36 cards) and questions on the back of each card to foster discussion; an A4-sized booklet with small versions of all the picture cards that women can take home to share what they’ve learned with their partners and families; an implementation guide for HEWs to introduce G-ANC in their HP; a simple G-ANC register to aid the facilitator to track attendance and record other data; and three monitoring tools, including a meeting observation checklist to provide feedback and assess fidelity. The picture cards were pretested with HEWs before the pilot phase, and all the intervention materials will be revised as needed based on the pilot feedback. Each intervention HP will be provided with 12 chairs; a basic set of supplies and commodities, including POCT reagents to run activities; two weigh scales; three user-friendly Microlife PSA blood pressure devices for the self-assessments; and one privacy screen to divide the private clinical consultation area from the larger G-ANC meeting space.

All clients will continue to receive the components of standard care, and no standard therapies will be denied to the intervention group. Likewise, standard, individual ANC care will not be denied if requested at any time.

**
*Training*
**: During time period one (T1: control period), two HEWs will be trained on community mobilization and gestational age estimation (including knowledge and skills) at selected HP for two days. During the intervention period, two HEWs per HP from intervention HP will be trained on G-ANC facilitation, gestational age estimation, and community mobilization for five days. From control HPs, two HEWs per HP will be trained on community mobilization and gestational age estimation for two days. Midwives from intervention HCs who will provide on-site mentorship to HEWs during G-ANC implementation will be trained for four days on G-ANC-focused mentorship by the study team (i.e., senior health professionals from Jhpiego Ethiopia with specialization in maternal health). Midwives from control HCs will be oriented for one half day on community mobilization, screening procedures, and linking women who come to the HC for their first ANC visit to HPs under their catchment. Key stakeholders, including participating health facility managers and regional managers, will be oriented to G-ANC to build ownership and support. Midwives from HC will provide mentorship, supervision, on-the-job support, guidance, and feedback to HEW as they implement G-ANC in their HPs.

### Outcomes

**
*Primary outcome 1*:** Proportion of women with at least four ANC visits.

**
*Primary outcome 2*:** Proportion of women who delivered in a health facility.

After exploring the balance by time period/intervention status and correlations, the effect of G-ANC will be estimated using generalized linear mixed effects models with binomial distribution and logit-link.

We will adjust for facility- and individual-level characteristics that show imbalance between the intervention versus control time periods and can be strongly correlated with the outcome scores. The primary analysis will not adjust for multiplicity and will be performed at 0.05 level of statistical significance.

**
*Secondary outcomes*:** Satisfaction level of women with ANC services, proportion of women who reported self-efficacy or empowerment.

Analysis of secondary outcome measures will follow a plan similar to the analysis of the primary outcome. Subgroup analysis will be conducted for specific subgroups to determine if the interventions were different. The key subgroups of interest are marital status, education, and economic status.

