### Sample size

We used the existing data from Amhara region for two primary study outcomes (i.e., four or more ANC contacts [31.5%] and facility-based delivery [27.1%]) to calculate the number of clusters (i.e., HCs) to be randomized to be able to detect an odds ratio of 2 comparing post-intervention to pre-intervention proportion with 80% statistical power using stepped-wedge design with three time periods and two steps for switching from standard care to intervention (
Figure 1). For the complete stepped-wedge design, the calculations indicate that a sample of 12 HCs with three time periods/two steps, six HCs switching from control to treatment at each step, and with an average of 30 women per cluster (i.e., three HPs with 10 women in each) per time period achieves 84% power to detect an odds ratio of 2 at 0.05 level of statistical significance. The underlying pre-intervention proportions and the post-intervention proportions associated with odds ratio of 2 are shown in
Table 4.

**Table 4. T4:** Pre-intervention and post-intervention proportions with associated odds ratio.

Study Outcome	Pre-Intervention Proportion, P2 ( Table 1)	Odds Ratio to be Detected	Post-Intervention Proportion, P1
Four or more ANC contacts	0.315 (Amhara)	2	0.48
Facility-based delivery	0.271 (Amhara)	2	0.43

The within-HC correlation (intraclass correlation coefficient [ICC]) is assumed to be 0.100. This level of correlation is consistent with the one reported by Ousman
*et al.*, where clustering was done at enumeration-area level with an ICC of 0.11 for ANC visits (
Ousman *et al.*, 2019). The total sample size for ANC clients is then 12 HCs x 3 HPs x 10 women/HP x two time periods = 720 women. An odds ratio of 2.0 translates to 50%–60% improvement in completion of four or more ANC contacts and 60%–70% improvement in facility-based delivery in the G-ANC arm compared to pre-intervention.

The study will be conducted in 12 HCs. The overall sample size is a total of 770 women. The pilot will enroll 50 women (i.e., 10 women per HP, five HPs), and the randomized control trials will include a maximum of 720 women (
Table 5). Sample size for the qualitative data collection is indicated in
Table 6.

**Table 5. T5:** Number of HCs, HPs, and women included in the G-ANC study.

	Pilot	Time parried 1 Control	Time Period 2 (control + intervention)	Time Period 3 (intervention)	Total
HC	2	6	12	6	**14**
HP	5	18	36	18	**41**
Women	50	180	360	180	**770**

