### Data collection

Both quantitative and qualitative data collection approaches will be used in this study. Data will be collected in the pilot phase and then during study implementation (Phase 2).

Once enrollment begins, all new ANC attendees in the selected HPs will be screened for eligibility during the first ANC contact with a health care provider. The screening and enrollment questionnaire will be completed. Basic demographic data will be collected from all eligible consented women (all who meet the inclusion criteria). All data will be de-identified for those who decline study participation. Baseline and endline data will be collected from all eligible and voluntary women participating in all study time periods. During the first period, data will be collected from 18 control HPs. In the second period (T2), data will be collected from 18 intervention and 18 control HPs. In the third period, (T3) data will be collected from 18 intervention HPs.

Data quality will be monitored through the use of trained research assistants and supervisors, data quality supervision, and use of an electronic data collection program to minimize data entry errors.

The study team will select respondents for the IDIs at the end of the study based on preliminary findings from the quantitative survey. IDIs with women will be conducted at the end of T2 and T3, after completion of all G-ANC meetings (
Table 7). Specific topics/domains to explore with G-ANC participants include satisfaction with care, any perceived changes in self-efficacy or empowerment, health literacy, improved communication and/or trust with providers and the health system as a whole, factors in uptake/non-uptake of postpartum family planning, and the overall impression of the G-ANC model. In this study, we will use standardized pretested tools to assess the levels of empowerment, self-efficacy, and satisfaction. For empowerment and self-efficacy, we will use eight questions related to their current pregnancy and calculate a composite score to understand the woman's level of empowerment. We will ask 11 questions about their satisfaction with the ANC received during their last pregnancy and with the G-ANC for their current pregnancy.

**Table 7. T7:** Data collection timing, per tool.

Data collection tool	Study participant	Timing of data collection		
		T1	T2	T3*
Cluster level information	HP level information	18 HPs	36 HPs	18 HPs

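### The empowerment/self-efficacy outcome is defined as a proportion of women although an eight-item composite score is collected; analysing the score would be more precise

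*Protocol article*

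**What the plan says.** The Outcomes section of the protocol article lists two secondary outcomes: how satisfied women are with their ANC, expressed as a level, and the "proportion of women who reported self-efficacy or empowerment". It adds that "Analysis of secondary outcome measures will follow a plan similar to the analysis of the primary outcome". The primary analysis, given there and again under Data analysis, uses "generalized linear mixed effects models with binomial distribution and logit-link", with intervention, time period and their interaction as predictors and a random intercept for HC.

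The Data collection section describes the instruments. The one for empowerment and self-efficacy is set out as follows: "we will use eight questions related to their current pregnancy and calculate a composite score", which is meant to show how empowered each woman is. For satisfaction, "We will ask 11 questions about their satisfaction with the ANC received during their last pregnancy", and the sentence goes on to cover G-ANC in the current pregnancy. That section also says the tools are standardized and pretested.

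The article gives no rule that turns the eight-item score into a proportion of women.

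**The concern.** One section defines the empowerment/self-efficacy outcome as a proportion; another measures it as a graded score. A composite score becomes a proportion of women only if each woman is classified from her score, and the article describes no other route. Following the text therefore means discarding the differences between women on the same side of the dividing value.

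The form of the outcome and the type of model are stated in the article, so this is more than a scoring detail left for later. A cut-off supplied elsewhere would make the proportion well defined, but it would not recover the lost information. At stake is the precision of one of only two listed secondary outcomes, in a trial with 12 clusters.

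Satisfaction raises a smaller point. It is called a level, so a binomial model does not carry over to it unchanged, and the article does not say what replaces that model.

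**Working it through.** **The plan's own figure.** The Sample size section claims 84% power for an odds ratio of 2 with 12 HCs, three periods, two steps, 30 women per HC per period and ICC 0.100, from baseline rates of 31.5% and 27.1%. A Hussey–Hughes calculation (fixed period effects, random HC intercept, total variance p0(1−p0), two-sided 0.05) gives 83.9% for four or more ANC contacts and 83.1% for facility delivery. The stated figure is reproduced. It concerns the primary outcomes only; the same variance model is used below.

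**Inputs.** From the Sample size section: ICC 0.10, 30 women per HC per period, six HCs per sequence. Assumed, because the documents do not give them: a normal score, the same ICC for this score, an intervention effect without a period interaction, and splits of 50/50, 25/75 and 16/84.

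**Step 1: individual-level efficiency.** For a normal score cut at c with a proportion p above it, the efficiency of the proportion relative to the score is φ(c)²/[p(1−p)].
- 50/50: 0.3989²/0.25 = 0.637
- 25/75: 0.3178²/0.1875 = 0.539
- 16/84: 0.2433²/0.1344 = 0.440

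**Step 2: ICC of the yes/no variable.** For two women in the same HC, the bivariate normal with correlation 0.10 gives a binary ICC of 0.064, 0.055 and 0.046 for the three splits.

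**Step 3: planned data collection.** Table 5 and the Study implementation section have the first six HCs contribute T1 (control) and T2 (intervention), and the second six contribute T2 (control) and T3 (intervention). With free period effects, T1 and T3 are each seen under one condition only, so the effect is identified from T2 (6 versus 6 HCs). The variance of an HC mean, in units of total variance, is ICC + (1−ICC)/30:
- score: 0.10 + 0.90/30 = 0.130
- proportion: 0.095, 0.087 and 0.078 for the three splits

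Retained efficiency is the Step 1 value times the ratio of these variances:
- 50/50: 0.637 × 0.130/0.095 = 0.87
- 25/75: 0.539 × 0.130/0.087 = 0.81
- 16/84: 0.440 × 0.130/0.078 = 0.73

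**Step 4: complete design.** If all 12 HCs contribute in all three periods, as the power statement assumes, the Hussey–Hughes variance of the effect is 0.01435 for the score. For the proportion it is 0.01458, 0.01458 and 0.01454, in units of its own total variance. Retained efficiency is 0.637 × 0.01435/0.01458 = 0.63, and likewise 0.53 and 0.43.

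| Split | Retained, planned collection | Retained, complete design |
|---|---|---|
| 50/50 | 0.87 | 0.63 |
| 25/75 | 0.81 | 0.53 |
| 16/84 | 0.73 | 0.43 |

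The loss is smaller under the planned collection because variation between HCs dominates a single-period comparison.

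**Step 5: what this means for power.** Under the planned collection the standard error for the score is √(2 × 0.130/6) = 0.208 SD, and power is Φ(d/0.208 × √efficiency − 1.96). The effect d is assumed.

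| Effect d | Score | 50/50 | 25/75 | 16/84 |
|---|---|---|---|---|
| 0.4 SD | 48.5% | 43.4% | 40.8% | 37.7% |
| 0.6 SD | 82.2% | 76.7% | 73.6% | 69.5% |
| 0.8 SD | 97.0% | 94.8% | 93.3% | 90.9% |

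Under the complete design, an effect that gives the score 80% power would give the proportion Φ(2.80 × √efficiency − 1.96), which is about 60%, 53% and 45% for the three splits.

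**The case against.** The strongest reply is that the article never says the score will be dichotomised. That is inferred from two sections of a condensed text. The secondary plan is only similar to the primary one, and because the same sentence covers a satisfaction level, it already leaves room for a model that is not binomial. A proportion with a pre-specified cut-off is also acceptable for a secondary outcome and easy for decision-makers to read. All of this stands and keeps the point minor. It does not remove the mismatch, because the outcome is named as a proportion and the measure is a score.

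A reader might infer three stronger things that the documents do not support.
- **That the cut-off is open and could be picked from the data, inflating type I error.** The trial is unblinded, and the Study status section reports that the T1 and T2 surveys have been conducted. It does not say that outcomes were analysed or that a threshold was unset. A scoring rule may stand in a statistical analysis plan or full protocol that is not shown, or come with the standardized tools.
- **That satisfaction is dichotomised too.** The article calls it a level and never a proportion.
- **That a linear model is certainly right.** Item format, score range and distribution are not given, and an eight-item score may be skewed or at ceiling.

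Nor do the study's conclusions on acceptability and empowerment rest on these outcomes alone. The in-depth interviews also explore satisfaction, self-efficacy and empowerment.

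**Conclusion.** The point holds as a minor one. The Outcomes and Data collection sections do not match on the empowerment/self-efficacy outcome, and following them together implies a yes/no reduction of a graded score. The loss is about 13% to 27% of the information under the planned data collection and about 37% to 57% under the complete design, for splits from 50/50 to 16/84. These figures rest on a normal score and on carrying over the ICC of 0.10, which the protocol sets for the primary outcomes. The power illustrations rest also on assumed effects. The size for the actual instrument cannot be fixed from the documents, but the direction is clear: the score is the more precise outcome and is already being collected.

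**What to change.** In the Outcomes section, name the eight-item empowerment/self-efficacy composite score as the secondary outcome. State that it is analysed with a linear mixed model, or an ordinal one if the score is skewed or at ceiling, with the same period, intervention and HC terms as the primary model. Keep the proportion of women as a supportive summary. Add that the 11-item satisfaction level is handled the same way.

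The cost is wording only: no new data, no change to the sample size and no change to the primary analysis. The small downside is that a score difference is less intuitive than a percentage; reporting the proportion alongside it covers this.

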### Recruitment and consent

ANC clients will be recruited via four strategies: 1) pregnant women will be identified in the community as potential study participants through existing local community structures (such as the women’s development army leaders) so that the study can be explained to potential participants and they can be linked them to an HEW for their first individual ANC contact and to a data collector; 2) all new ANC attendees in the intervention HPs will be screened for eligibility during the first ANC contact with an ANC service provider; 3) women who come to the HC for their first ANC visit will receive their first individual ANC visit at the HC and then be linked to a catchment HP for eligibility assessment and enrollment if they consent to participate; and 4) eligible women will be identified by G-ANC-trained HEWs who make door-to-door visits in the community.

Research assistants will rotate among each of the intervention HPs during the recruitment period to explain the study to women who meet the inclusion criteria and agree to participate in the study.

The research assistants will obtain verbal consent from women in a private space in the HP using institutional review board (IRB)-approved recruitment and consent documents in the local language. Verbal consent will be sought instead of written consent as written consent is seen as a personal identifier in the community and verbal consent is preferred. This consenting method was approved by the ethics committee (see Ethics section). The potential G-ANC participants will be informed during the consenting process of the expected number of meetings (i.e., ANC visits) and their rights, risks, and benefits. The research assistant will explain the need to collect their names, phone numbers, and addresses, which will be used for study-related follow-up purposes only. Anyone declining participation in the study will be referred to individual ANC care during the intervention period. A baseline questionnaire will be administered to consenting study participants at the beginning of each step (time period).

For HEWs and health facility managers, study staff will explain the purpose based on the inclusion criteria. The HEWs will be oriented to the study including the randomization (they will not be blinded to the order of randomization of their HC and affiliated HPs) and their role in the study including screening first-time ANC clients for eligibility to participate. HEWs who will be facilitating G-ANC meetings will be informed that they may be asked to participate in an in-depth interview (IDI) at the end of the study related to implementation of group-based care and its effect on their job and satisfaction levels. Oral consent will be obtained in a private location at the health facility by research assistants.

For the regional health managers, study staff will contact the regional health bureau responsible for overseeing reproductive health programs in the Amhara region via phone or in-person and invite the regional health manager to participate in an IDI as per the inclusion criteria. An appointment will be scheduled to obtain informed consent and conduct the IDI, preferably at the regional health bureau office. Written consent will be obtained by the research assistant who will conduct the interview in a private location.

For the IDIs of women and HEWs involved in G-ANC, qualitative data will be collected at the end of the study after all G-ANC meetings have been conducted. Oral consent will be obtained from the HEWs and eligible women three to six months postpartum to be enrolled in the qualitative portion of the study.

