### Randomization

Health centers with catchment HPs that provide POCT for ANC services will be listed and randomized to begin the intervention at T2 (i.e., the first randomized set of facilities) or T3 (i.e., the second randomized set of facilities). These facilities will be randomized 1:1 before T1 to two different intervention start times (i.e. two sequences), stratified by location and client volume, using randomly permuted blocks of size 2 and 4. We will use centralized randomization as the allocation concealment mechanism. A remote and independent statistician in the Johns Hopkins Bloomberg School of Public Health (JHSPH) will generate and implement the allocation sequence, and communicate it to the study sites after confirming the eligibility of the clusters. Health extension workers will identify pregnant women and provide the list of women to Addis Continental Institute of Public Health (ACIPH). ACIPH field workers will take consent and enroll eligible women.

**
*Blinding*:** Study staff and those assessing outcomes will not be blinded to knowing the study time period to which facility is randomized. The participants will also not be blinded about the type of care they will be receiving (G-ANC or routine/conventional care).

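### As worded, door-to-door recruitment can run only in intervention periods, so the mix of routes by which women are found changes with the condition

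*Protocol article*

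**What the plan says.** Recruitment and consent names four routes:

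1. identification in the community through existing structures such as women's development army leaders;
2. screening of new attendees, stated for intervention health posts (HPs);
3. linking to an HP of women whose first visit is at the health center (HC);
4. household visits: "eligible women will be identified by G-ANC-trained HEWs who make door-to-door visits in the community".

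The next paragraph adds: "Research assistants will rotate among each of the intervention HPs during the recruitment period".

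The Training paragraph under Intervention sets out who is trained in what.

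- In T1: "two HEWs will be trained on community mobilization and gestational age estimation (including knowledge and skills) at selected HP for two days".
- In the intervention period: "two HEWs per HP from intervention HP will be trained on G-ANC facilitation, gestational age estimation, and community mobilization for five days".
- In the same period: "From control HPs, two HEWs per HP will be trained on community mobilization and gestational age estimation for two days".
- For control midwives: "Midwives from control HCs will be oriented for one half day on community mobilization, screening procedures, and linking women who come to the HC" for a first visit to HPs in the catchment.

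Two other sections are worded without an arm limit. Randomization says: "Health extension workers will identify pregnant women and provide the list of women". Data collection says: "all new ANC attendees in the selected HPs will be screened for eligibility during the first ANC contact". Study implementation and Table 7 plan enrolment and surveys of control women, 180 of them in T1.

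**The concern.** The Study design section says that the main difference between conditions is individual versus group care, given in the same setting by the same staff. A recruitment route that exists under only one condition adds a second difference. HCs are randomized before T1 and women are enrolled afterwards, by a process that starts with health extension workers (HEWs) who know their place in the sequence. Randomizing the start time does not protect against identification that changes with the condition.

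Both primary outcomes are open to this. Women found at home may differ from women found by other routes in distance, in inclination to seek care and in gestational age at entry. The first two bear on four or more visits and on facility delivery. Gestational age bears directly on the visit count, because a woman found earlier has more time to reach four. These influences can pull in opposite directions.

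**Working it through.** **Step 1: who can carry out each route under each condition, as worded**

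| Route or activity | Intervention period | Control period |
|---|---|---|
| 1. Community structures | Yes | Yes, no arm limit |
| 2. HP screening | Yes | Not in Recruitment and consent; yes in Data collection |
| 3. Linking from HC | Yes | Yes; control midwives are oriented to do it |
| 4. Household visits by G-ANC-trained HEWs | Yes | No one has that training |
| Research assistants' rotation | Yes | Not in Recruitment and consent, yet control women must be consented and surveyed |

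Row 2 is repaired by Data collection. The last row cannot be meant literally, since Study implementation and Table 7 need 180 control women in T1. Row 4 is not repaired. Randomization has HEWs in general identify women but does not mention household visits, and nothing else extends that route to control periods.

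**Step 2: the planned effect, for scale**

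An odds ratio of 2 on a pre-intervention proportion p0 gives p1 = 2o/(1 + 2o), with o = p0/(1 − p0).

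- Four or more visits: o = 0.315/0.685 = 0.460, so p1 = 0.920/1.920 = 0.479. Table 4 gives 0.48.
- Facility delivery: o = 0.271/0.729 = 0.372, so p1 = 0.743/1.743 = 0.426. Table 4 gives 0.43.

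Table 4 is reproduced. The planned difference in four or more visits is 0.48 − 0.315 = 0.165.

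**Step 3: what a difference in routes could do (assumed inputs)**

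The article gives neither the share of women entering by each route nor how those women differ. Let f be the share of the intervention cohort found at home, with none in controls. Let k be the ratio of their outcome odds, without any intervention, to those of other women. Assume no true effect.

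- Proportion among home-found women: q = k·o/(1 + k·o)
- Intervention proportion: m = (1 − f)·p0 + f·q
- Apparent odds ratio: [m/(1 − m)]/o

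Worked case with p0 = 0.315, f = 0.25 and k = 2: q = 0.479; m = 0.75 × 0.315 + 0.25 × 0.479 = 0.356; apparent odds ratio = (0.356/0.644)/0.460 = 1.20. With k = 0.5: q = 0.187, m = 0.283 and the ratio is 0.86.

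| f | Four or more visits, k = 0.5 to 2 | Facility delivery, k = 0.5 to 2 |
|---|---|---|
| 10% | 0.94 to 1.08 | 0.94 to 1.08 |
| 25% | 0.86 to 1.20 | 0.86 to 1.21 |
| 50% | 0.73 to 1.43 | 0.73 to 1.44 |

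If a share g of controls was also found at home, the shift in the proportion is (f − g)(q − p0), where p0 is the proportion among the other women. It shrinks as the routes converge and vanishes when g = f.

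**The case against.** The strongest reply is that Recruitment and consent is loosely written from the intervention side. It must be wrong about the research assistants, so its description of the household visitors may be equally loose. The text never says that only G-ANC-trained workers visit homes; that follows from the training description. The Introduction says HEWs are expected to spend 75% of their time in communities, so control HEWs may have visited homes anyway. This is a fair argument about what was done. It does not rescue the text: if control HEWs did visit homes, the section misdescribes the procedure and needs the same correction.

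A reader might go further and infer that control cohorts contain no actively sought women, or that the two groups come from different source populations. The article does not support either. Route 1 seeks women in the community with no arm limit, control HEWs are trained in community mobilization, and control midwives are oriented to it. Each HP supplies both its control and its intervention cohort, so the catchment is the same. What differs is the mix of routes within it.

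A reader might also infer that HEWs pick their most reliable clients for the eight to 10 places. The article does not cap the HEW's list, separate field workers obtain consent and enrol, and an order of entry is a detail that the full protocol may contain.

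The planned adjustment for imbalanced facility and individual characteristics gives partial protection. It cannot reach unmeasured differences such as inclination to seek care.

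**Conclusion.** The point holds in a limited form. As worded, one of four routes can operate only in intervention periods. Two further activities, HP screening and the research assistants' rotation, are tied to intervention HPs in conflict with Study implementation, Data collection and Table 7. If the plan was followed as written, the way women were found changed with the condition, under unblinded HEWs, and both primary outcomes can be biased.

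The documents fix neither the size nor the sign. On the assumptions above the bias is small at a 10% share and material at 50%, where a null effect could appear as an odds ratio from about 0.73 to about 1.44. Those ranges rest on assumed shares and odds ratios and on no household finding in controls, so they overstate the shift if control HEWs also visited homes. None of the assumed cases reaches the target odds ratio of 2. The text should be corrected and the exposure measured; this does not show that the trial's comparison is invalid.

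**What to change.** **Text.** Reconcile Recruitment and consent with Training, Randomization and Data collection so that the same routes apply in control and intervention periods. In route 4, refer to HEWs in all study HPs; in route 2 and the research assistants' rotation, refer to all study HPs.

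**Conduct.** Study status (September 2024) reports the T1 and T2 surveys as done and T3 in preparation, and the core T3 data collection is intervention only. Adding household visits to control posts can therefore no longer change a control cohort. What remains open:

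- document the routes actually used for control and intervention women in T1 and T2;
- recruit the T3 intervention cohorts by the routes that were used for the T2 controls in the same posts;
- record route of entry in Tool 1a.

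**Analysis.** Where route can be recovered, add a sensitivity analysis that excludes household-identified women or adjusts for route. Adjustment is informative only if both conditions contain such women; otherwise use exclusion. Exclusion is itself approximate, because some women found at home would have entered by another route.

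**Cost.** One form field, one extra analysis, and possibly slower T3 recruitment if household visits were not used for the controls.
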